## Abstract

**Background:**

Treatment of superficial venous reflux has been shown to improve ulcer healing time and reduce the risk of ulcer recurrence. Terminal ablation of the reflux source (TIRS) is an alternative to formal endovenous ablation or surgery which can be performed by injecting sclerosant foam into the peri-ulcer plexus of the veins. TIRS has been shown to be successful and in our experience is the option preferred by many patients, when offered as an alternative to axial ablation (AA).

**Aim:**

To determine if the proportion of ulcers healed within 6 months of endovenous treatment differs between patients undergoing AA of varicose veins or TIRS by peri-ulcer foam sclerotherapy.

**Methods:**

AAVTIRS is an assessor-blinded randomised controlled trial. Patients will be recruited from a dedicated ulcer clinic in Roscommon University Hospital and from the vascular surgical clinics in University Hospital Galway. All patients attending the ulcer clinic will be screened for eligibility.

**Randomisation:**

Random computer-generated sequence is stratified by ulcer size. Allocation will be concealed using sealed opaque envelopes.

**Blinding:**

Assessors reviewing wounds at follow -p visits will be blinded to patient allocation.

**Primary endpoint:**

The proportion of ulcers healed within 6 months of enrolment.

**Discussion:**

This will be the first time that TIRS has been evaluated with a properly powered randomised trial in the setting of venous ulcer management. Streamlining the management of venous ulcers has broad health economic benefits. If it is found that TIRS is superior or non-inferior to AA, then a less expensive, less invasive injection can be offered as an alternative to AA in an attempt to encourage the healing of venous ulcers. If AA is found to be superior to TIRS, then this would suggest that all patients undergoing ablation in the management of venous ulcers should have their superficial reflux fully treated, building on the evidence of the EVRA trial.

**Trial registration:**

ClinicalTrials.gov NCT04484168. Registered on 23 July 2020

**Supplementary Information:**

The online version contains supplementary material available at 10.1186/s13063-022-06440-4.

## Administrative information

**Table Taba:** 

**Trial synopsis**	
**Title**	Axial ablation versus terminal interruption of the Reflux Source in venous ulcer management: a randomised controlled trial in venous ulcer management
**Public title**	AAVTIRS trial
**Medical condition under investigation**	Lower limb venous ulcers
**Purpose of trial**	To evaluate whether there is a clinically significant difference between axial ablation of varicose veins and peri-ulcer terminal interruption of the reflux source in promoting healing of lower limb venous ulcers.
**Primary objective**	To determine if the proportion of ulcers healed within 6 months of endovenous treatment differs between patients undergoing axial ablation of varicose veins or terminal interruption of the reflux source by peri-ulcer foam sclerotherapy.
**Secondary objectives**	To determine whether there is a significant advantage to either treatment, in a reduction in ulcer size, encouraging wound regeneration, and venous disease severity or a significant difference in patient-assessed quality of life, between the two interventions
**Trial design**	Prospective single-centre assessor-blinded randomised controlled trial
**Primary endpoint**	Proportion of ulcers healed within 6 months of intervention
**Secondary endpoints**	Absolute and relative reduction in ulcer size Time to ulcer healing BWAT score progression VCSS progression over time Change in Charing Cross Venous Ulcer Questionnaire score from treatment to completion of follow-up
**Sample size**	320 individual ulcers
**Summary of eligibility**	Patients with a leg ulcer, attributable to venous insufficiency, without any contraindication to compression or either of the comparator treatment modalities will be included.
**Screening process**	All patients with a venous ulcer attending a Leg Ulcer Centre Ireland—a dedicated venous ulcer assessment clinic in Roscommon University Hospital will be considered for enrolment.
**Randomisation**	Affected legs will be randomised in a 1:1 ratio to axial ablation or terminal interruption of the reflux source.
**Treatment**	Patients will be treated on the same day as randomisation according to their assignment to either group
**Follow-up**	Patients will be followed monthly for 6 months.
**End-of-study**	The trial will end when all patients have been enrolled and completed both treatment and 6-month follow-up.
**Safety monitoring**	The principal investigator will be notified of any serious adverse events, and they will liaise with all investigators and the ethics committee.
**Criteria for stopping trial on safety grounds**	Unacceptable risk to participants due to unexpected serious adverse events Unacceptable rate of adverse events Interim demonstration of a significant difference in efficacy Interim demonstration of a significant difference in the rate of adverse or serious adverse events Intolerable discomfort during treatment or compression, or inability to adhere to the protocol for any other safety-related reason leading to insufficient compliance with randomisation
**Registration**	ClinicalTrials.gov registration NCT04484168. Registered on 23/7/2020
**Recruitment**	Commenced on 21 July 20—ongoing. Planned completion 1st quarter of 2022, last patient last visit 3rd quarter of 2022
**Recruiting country**	Ireland
**IPD sharing**	Not planned
**Funding**	No funding has been received for this research.
**Ethics**	Approved by the Galway University Hospitals Clinical Research Ethics Committee 18 June 2020, ref. no. C.A. 2416

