### Randomisation

Once enrolled, patients will be stratified by ulcer size (< 5 cm^2^, 5.1 to 10 cm^2^, 10.1 to 25 cm^2^, > 25 cm^2^) and will be randomised to either arm on a 1:1 basis.

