#### Implementation

On enrolment the principal investigator will assign a trial number to the patient and be informed of the ulcer’s size. An envelope will then be taken from the appropriate stratum. The trial number will be written on the envelope, and the envelope passed to the surgical team. The team performing the procedure will sign the envelope sealed, and open it in the operating room immediately before the procedure. A member of the surgical team will then take appropriate consent from the patient for the specific procedure being carried out.

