### Sample size

Power calculation [25] was informed by existing evidence [11–13, 15], predominantly the EVRA trial [15]. EVRA showed a 95% success rate for ulcer healing at 24 weeks. We anticipated a more modest success rate because our exclusion criteria did not limit participants to those with new ulcers. In addition, TIRS has very limited existing evidence with reporting healing ranging from 83 to 100% [21, 23]. An 80% success rate was felt to be reasonable for both treatments in a non-inferiority trial. A cohort of 308 patients (154 per arm) was required to ensure that if the null hypothesis should be rejected, the limits of a two-sided 90% confidence interval would exclude a difference between the groups of more than 15%, with 90% power at 5% significance level.

Given that existing evidence for TIRS consists mainly of small case series with widely varying healing rates, we planned once the first 50 cases exited the trial (either healed or completed 6 months of follow-up) as a pilot to inform a further power calculation for both superiority and non-inferiority outcomes.

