### Exclusion criteria

Patients will be excluded if any of the following apply:Pregnancy (or breastfeeding and needing to feed within 48 h of treatment).Active infection of ulcer, or infection within the last 2 weeks.Leg ulcer of non-venous aetiology as determined by clinical assessment.Isolated perforator vein reflux only.Evidence of deep venous insufficiency or thrombosis.Known hypersensitivity to Sotradecol or similar sclerosants.Previous inability to tolerate compression bandages.Presence of any contraindications for the use of compression bandages:Absence of a palpable pulse, and Ankle Brachial Index (ABI) < 0.8Decompensated congestive cardiac failure (NYHA class IV)Known hypersensitivity to any of the component materialsPatients unable to provide informed consent.Patients attending the leg ulcer clinic already will be excluded from enrolment with the same ulcer but will be eligible to enrol with a contralateral ulcer. Recurrent ipsilateral ulcers will not be excluded.

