#### Deferred enrolment

Patients wishing to take time to think about enrolment will be offered the chance and brought back to the clinic at an interval agreeable to them.

Patients already attending the ulcer clinic will be eligible for enrolment if they present with a new contralateral ulcer.

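### The protocol contradicts itself on whether patients, legs or ulcers are randomised and counted, and its named tests make no provision for two ulcers from one patient

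*Protocol article*

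**What the plan says.** All references are to the Protocol article.

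- **Trial synopsis:** the sample size is "320 individual ulcers", and "Affected legs will be randomised in a 1:1 ratio to axial ablation or terminal interruption of the reflux source".
- **Randomisation:** "Once enrolled, patients will be stratified by ulcer size", and it is these patients who "will be randomised to either arm on a 1:1 basis".
- **Implementation:** "On enrolment the principal investigator will assign a trial number to the patient and be informed of the ulcer’s size". That is one number per patient and one ulcer size to choose the stratum.
- **Sample size:** "A cohort of 308 patients (154 per arm) was required".
- **Primary outcome:** a proportion of ulcers healed at the 24-week review.
- **Deferred enrolment:** "Patients already attending the ulcer clinic will be eligible for enrolment if they present with a new contralateral ulcer". The Exclusion criteria say the same of contralateral ulcers and add "Recurrent ipsilateral ulcers will not be excluded".
- **Statistical analysis:** chi-squared and Fisher's exact tests for categorical variables, Student's t and Mann-Whitney tests for continuous ones. Analysis is by intention to treat, with a per-protocol analysis as well. Neither this section nor any other mentions an index ulcer, a one-entry rule, or an allowance for several ulcers in one patient.

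**The concern.** The unit of randomisation is fixed when an envelope is drawn, and the recruitment target is counted in some unit from the first enrolment. A later analysis plan cannot settle either in retrospect. Here the target is in ulcers in one place and in patients in another, and allocation is by leg in one place and by patient in another.

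This matters because two ulcers on one person share that person's general health, adherence to compression and community nursing, so their outcomes are likely to be correlated. The four named tests ignore that. Whether the resulting interval is too narrow, about right or too wide depends on whether the two ulcers fall in the same arm, and the protocol does not settle that.

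Patient-level outcomes raise a separate difficulty. The CCVUQ is a patient questionnaire, and the VCSS includes signs and symptoms outside the wound. If a patient has one leg in each arm, the effect of one treatment may carry over into scores attributed to the other.

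**Working it through.** **1. Reproducing 308.** Inputs from the Sample size section: 80% healing in both arms, a 15-point margin, a two-sided 90% confidence interval, 90% power. For equivalence by two one-sided tests with a true difference of zero:

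n per arm = 2 × 0.8 × 0.2 × (1.645 + 1.645)² / 0.15² = 153.9, so 154 per arm and 308 in total.

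The stated figure is reproduced. The formula takes 308 independent units.

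**2. From 308 to 320.** 320/308 = 1.039. If the difference were dropout, it would be 1 − 308/320 = 3.75%, but no dropout or clustering allowance is stated, and the unit changes between the two figures. With 320 independent units (160 per arm), power would be 91.3%. If 10% of patients gave two ulcers, 320 ulcers would come from 320/1.10 ≈ 291 patients, fewer than the 308 required.

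**3. Both ulcers in the same arm.** The protocol gives neither the fraction f of patients with two ulcers nor the within-patient correlation (ICC). I assume f = 10-30% and ICC = 0.3-0.7.

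- Share of ulcers with a partner: s = 2f/(1 + f)
- Design effect: DE = 1 + s × ICC
- Unadjusted one-sided error: Φ(−1.645/√DE)
- Unadjusted power: 2Φ[(0.15/SE − 1.645)/√DE] − 1
- Cluster-adjusted power: 2Φ[0.15/(SE√DE) − 1.645] − 1

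At 160 per arm, SE = √(0.32/160) = 0.0447.

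| f, ICC | s | DE | 320 ulcers worth | Error, unadjusted | Power, unadjusted | Power, adjusted |
|---|---|---|---|---|---|---|
| 10%, 0.3 | 0.182 | 1.05 | 303 | 5.5% | 90.4% | 89.5% |
| 20%, 0.5 | 0.333 | 1.17 | 274 | 6.4% | 88.6% | 85.6% |
| 30%, 0.7 | 0.462 | 1.32 | 242 | 7.6% | 86.3% | 79.6% |

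The error column and the adjusted-power column belong to different analyses. An adjusted interval holds the error at about 5% and pays in power; an unadjusted one keeps more power and pays in error.

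**4. Other allocation patterns.** Simulation of the unadjusted 90% interval used 308 ulcers, 10-30% of patients with two ulcers, a latent correlation of 0.7 (a correlation of about 0.46 between the binary outcomes) and 8,000 trials per setting.

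| Allocation of a patient's two ulcers | Error | Power |
|---|---|---|
| Same arm | 0.059-0.065 | 0.89-0.86 |
| Each leg randomised independently | 0.050-0.052 | 0.89-0.90 |
| Opposite arms | 0.043-0.036 | 0.91-0.93 |

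The synopsis wording points to the second row if each leg is drawn independently. The Randomisation wording points to the first row if a patient's allocation carries over to a later ulcer.

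**The case against.** The strongest reply is that the synopsis randomises legs, and if each leg is drawn independently the unadjusted test is close to nominal. That stands. A reader might infer that the interval must be too narrow and equivalence too easily declared. The documents do not support this without the condition that a patient's ulcers share an arm.

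The number of patients with two ulcers may also be small. With f = 5% and ICC 0.3, DE is 1.03, the error is 5.2%, and 320 ulcers are worth 311 independent ones, still above 308. This stands too: the ranges above are assumptions, and the protocol offers nothing to narrow them.

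Two further inferences go beyond the text:

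- **A leg that heals, recurs, re-enters and counts as two successes.** The Inclusion criteria admit primary or recurrent ulcers, so the sentence on recurrent ipsilateral ulcers may refer only to recurrence before entry. Re-entry is not barred, but it is not described either. Contralateral entry is the better-supported route.
- **A patient with a leg in each arm having only one CCVUQ score.** The questionnaire is completed at the initial visit and at exit, and a new contralateral ulcer may enter later with its own questionnaires. Carry-over between arms is possible; a single shared score is not stated.

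Finally, cluster adjustment is the kind of detail often left to an analysis plan, and none is shown here. That covers the choice of method. It does not cover the conflict over the unit, which lies within the current protocol text.

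**Conclusion.** The contradiction over the unit is certain: ulcers and legs in the synopsis, patients in Randomisation, Implementation and Sample size, ulcers in the primary outcome. The figure of 308 holds for independent units, and 320 does not follow from the same inputs.

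The statistical consequence is conditional. If a patient's ulcers share an arm, and under the assumed ranges, the unadjusted test runs modestly above 5% and power falls somewhat below the 91.3% that 320 independent units would give; only the adjusted analysis at the extreme of the range reaches about 80%. Under independent randomisation of legs the effect is negligible, and under split allocation the test is conservative. Since the protocol does not settle which pattern applies, its stated error rate and power cannot be confirmed. The matter should be corrected, but it does not by itself invalidate the trial.

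**What to change.** State one unit of randomisation and analysis in the Trial synopsis, Randomisation and Sample size sections, and reconcile 308 with 320 in that unit, naming any allowance that links them. Then choose one of two routes:

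1. **One index ulcer per patient**, taken as the first randomised entry, for the primary analysis. Further ulcers go into a secondary analysis clustered by patient.
2. **Legs or ulcers kept as the unit**, with a patient-clustered confidence interval (GEE or robust standard errors) for the primary risk difference.

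If legs have in fact been randomised, the second route sits better with intention to treat, because the first leaves randomised legs out of the primary analysis.

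Under either route, use first entries only for the CCVUQ, and state whether a recurrent ulcer in a previously enrolled leg can enter again.

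The cost is a change of wording and one clustered analysis. The price is a slightly lower effective sample size under the first route or, where a patient's ulcers share an arm, a slightly wider interval under the second. The protocol reports enrolment as ongoing, so this can be settled before the final analysis.

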## Background

Venous ulceration poses a massive burden on health services internationally [1–4]. In Ireland, the prevalence of leg ulcers is 1 per 800 people in the general population, rising to 1 per 100 over the age of 70 years [1]. Compression therapy has been shown to expedite the healing of venous ulcers [5, 6]. However, it is time-consuming for patients and practitioners and requires significant community support.

Superficial venous reflux is frequently present in patients with venous leg ulcers [7]. Surgical treatment of varicose veins, in combination with compression, has been shown to improve the rate of ulcer recurrence, but the ESCHAR trial did not show any benefit in ulcer healing from surgery [8, 9]. Therefore, many guidelines only recommend surgery as a means to reduce recurrence [10]. Numerous observational studies [11–14] and in particular the Early Venous Reflux Ablation (EVRA) trial have demonstrated that after endovenous treatment of reflux, ulcers do tend to heal faster, reducing ulcer persistence at 6 months [15]. This has important implications both for the patient in the psychosocial burden of venous ulceration [16] and for the economic burden of ulcer management on community, outpatient and inpatient services.

Endovenous management of reflux is achieved by ablation of the main superficial veins of the leg, or axial ablation (AA). If incompetent, the long or short saphenous veins, or their larger tributaries, contribute to venous ulceration by raising venous pressure, and therefore capillary hydrostatic pressure, leading to oedema, relative under-perfusion and hypoxia, and triggering an inflammatory cascade [17]. AA encourages healing by reducing venous reflux, decreasing venous pressure in distal veins, which improves the perfusion pressure at the capillary level. This improves oxygen and nutrient delivery to ulcerated areas, facilitating wound healing. Terminal interruption of the reflux source (TIRS) aims to target those veins in the distal leg which are directly responsible for transmitting the raised venous pressure to the ulcerated area and, by only treating these specific veins, achieve the necessary improvement in perfusion locally. While a review of the level 1 evidence has shown less anatomical success with ultrasound-guided foam sclerotherapy, clinical success was similar [18]. Foam sclerotherapy has been shown to be safe and effective in the management of venous ulcers [19, 20]. The ability to deliver foam via a small needle without anaesthetic makes foam sclerotherapy ideal for TIRS, and studies of perilesional sclerotherapy have found it to be safe and effective [21–23].

## Treatments

### TIRS

TIRS will be achieved using foam sclerotherapy. This involves ultrasound assessment of the ulcerated area and identification of veins which allow reflux into the ulcer itself. Under ultrasound guidance, a small needle is used to inject a sclerosant foam directly into those veins identified for treatment. The sclerosant Sotradecol (sodium-tetradecyl-sulphate) will be used for all patients in the trial. The liquid form of Sotradecol will be made into foam by agitating 1-ml Sotradecol with 4 ml air in two 5-ml syringes in a modified Tessari method [24].

### Axial ablation

All patients randomised to AA will have mechanical occlusion with chemical assistance (MOCA). Because this technique is non-thermal, it can be used in more superficial veins, facilitating use in a wider range of anatomies than a thermal technique. Clarivein™ (Vascular Insights LLC, Quincy, USA) is a device consisting of a rotating wire within a catheter. The catheter allows the infusion of sclerosant, while the rapid rotation of the wire scores the intima of the vein, generating an inflammatory response. The infusion of the sclerosant via the same catheter as the wire ensures that it is spread around the full circumference of the vein by the wire as it rotates, further augmenting the inflammatory response, causing occlusion of the vein initially, followed by obliteration. Sotradecol will also be used as the sclerosant in these patients.

## Aim

The aim of this trial is to answer the following research question.

In adult patients with venous ulcers, are TIRS and AA equivalent in their ability to increase the proportion of ulcers that heal completely within 6 months of treatment?

Null hypothesis: there is a clinically significant difference in ulcer healing.

Alternative hypothesis: there is no clinically significant difference in ulcer healing.

## Objectives

### Primary objective

The primary objective is to determine if the proportion of ulcers healing within 6 months of treatment with AA of varicose veins by MOCA or TIRS by peri-ulcer foam sclerotherapy is equivalent.

### Secondary objective

The secondary objective is to determine if there is a significant difference between the two treatments in:Absolute reduction in ulcer sizeRelative reduction in ulcer sizeTime to ulcer healing, in those patients whose ulcer has fully healed by the end of the trialWound regenerationObjective venous disease severityPatient-assessed quality of life

## Methods

### Statement of trial design

This is a prospective, assessor-blinded randomised controlled trial. The primary trial centre will be Leg Ulcer Centre Ireland operating in Roscommon University Hospital, with oversight from the Department of Vascular Surgery, University Hospital Galway (UHG). Other centres may come on board in the future.

### Randomisation

Once enrolled, patients will be stratified by ulcer size (< 5 cm^2^, 5.1 to 10 cm^2^, 10.1 to 25 cm^2^, > 25 cm^2^) and will be randomised to either arm on a 1:1 basis.

#### Sequence generation

Randomisation will be done using a computer-generated random number sequence, stratified by ulcer size.

#### Allocation concealment

Randomisation will be performed using sealed opaque envelopes containing treatment allocation, sequentially marked within each stratification level, to be opened by the operating surgeon immediately before intervention.

#### Implementation

On enrolment the principal investigator will assign a trial number to the patient and be informed of the ulcer’s size. An envelope will then be taken from the appropriate stratum. The trial number will be written on the envelope, and the envelope passed to the surgical team. The team performing the procedure will sign the envelope sealed, and open it in the operating room immediately before the procedure. A member of the surgical team will then take appropriate consent from the patient for the specific procedure being carried out.

